## Abstract

Critical care healthcare professionals are at high risk in developing burnout and mental health disorders including depression, anxiety, and post-traumatic stress disorder. High demands and the lack of resources lead to decreased job performance and organizational commitment, low work engagement, and increases emotional exhaustion and feelings of loneliness. Peer support and problem-solving approaches demonstrate promising evidence as it targets workplace loneliness, emotional exhaustion, promotes work engagement, and supports adaptive coping behaviors. Tailoring of interventions have also shown to be effective in influencing attitudes and behavior changes, attending to the individual experience and specific needs of end-users. The purpose of this study is to assess the feasibility and user-perceived acceptability of a combined intervention (Individualized Management Plan (IMP) and Professional Problem-Solving Peer (PPSP) debrief) in critical care healthcare professionals. This protocol was registered in the Australian and New Zealand Clinical Trials Registry (ACTRN12622000749707p). A two-arm randomized controlled trial, with pre-post-follow-up repeated measures intergroup design with 1:1 allocation ratio to either 1) treatment group–IMP and PPSP debrief, or 2) active control group–informal peer debrief. The primary outcomes will be conducted by assessing the recruitment process enrolment, intervention delivery, data collection, completion of assessment measures, user engagement and satisfaction. The secondary outcomes will explore preliminary effectiveness of the intervention using self-reported questionnaire instruments from baseline to 3-months. This study will provide the interventions’ feasibility and acceptability data for critical care healthcare professionals and will be used to inform a future, large-scale trial testing efficacy.

## Introduction

Wellbeing is a combined definition of feeling good and functioning well [1]. It can be conceptualized as a spectrum with high wellbeing, flourishing, and happiness at one end, and low wellbeing, increased anxiety, and depression at the other end [2]. High wellbeing portrays the experience of positive emotions and having a sense of purpose and control [1]. It is a sustainable condition that enables individuals to develop within their environment and thrive [3]. Individuals with high wellbeing in the workplace demonstrate optimal workplace engagement, productivity, and performance [3, 4]. Work engagement is characterized by dedication, vigor, and absorption [5, 6]. It is an indicator of intrinsic motivation and general autonomy within the workplace [6]. Unlike intrinsic motivation that focuses on one job task, work engagement reflects on a more pervasive and persistent affective-cognitive state [6]. Engaged workers will feel enthusiastic, energized, and will want to genuinely work [5, 6]. These workers facilitate positive organizational outcomes as they transcend employment expectations [6].

Burnout and work engagement are negatively associated and influence mental and physical health [5, 7]. Burnout is a prolonged response caused by chronic exposure to interpersonal stressors within the workplace [8]. Maslach and Leiter (2016) defined burnout as a psychological syndrome consisting of three dimensions: exhaustion, feelings of cynicism, and having a sense of ineffectiveness [8]. Exhaustion was described as the loss of energy, wearing out, depletion, fatigue, and debilitation, whereas cynicism portrays irritability, withdrawal, inappropriate attitudes towards patients, and loss of idealism [8]. Inefficacy was depicted as low morale, reduced capability or productivity, and the inability to cope [8]. Burnout and work engagement are influenced by job characteristics, which can be conceptualized by the job demands and job resources model (Job Demands-Resources (JD-R) model) [7, 9]. Job demands are energy-depleting aspects of the job that requires emotional, physical, and cognitive efforts—for example, workload, role stress, and work pressure [5, 9]. When employees are exposed to high job demands, they become chronically exhausted and psychologically distances themselves from their work [9]. Available and adequate job resources may psychologically fulfil the needs of employees and buffer the effects of high job demands on burnout [5, 9]. Job resources aims to achieve work goals and encourage personal development and growth [5, 9]. The JD-R model also considers the use of personal resources to attend to job demands [9]. Personal resources refers to self-beliefs, for example, the development of self-efficacy, optimism, and resilience—as it motivates employees to achieve work-related goals, which improves their wellbeing and job performance [9].

Healthcare professionals encounter high workload, adversities, and stress on a daily basis, which makes them vulnerable to burnout [10]. While burnout is experienced by healthcare professionals in general, the critical care workforce has been identified to be at heightened risk [11]. This is because critical care healthcare professionals are exposed to difficult daily workloads, high patient trauma, mortality, tragedy, and encounter challenging ethical situations on a daily basis [12]. The coronavirus 2019 (COVID-19) global pandemic has added a greater magnitude of strain on the critical care workforce with higher patient acuity, mortality rates, and struggles for personal safety [13]. National leaders have raised concerns regarding the impact of COVID-19 on the workforce’s wellbeing [13]. A systematic review of critical care healthcare professionals revealed 49.3% to 58% of the workforce experienced burnout and many suffer from mental health disorders [14]. Another cross-sectional study demonstrated 41% of intensive care workers had low wellbeing and 46% had peritraumatic distress [11]. Psychiatric morbidities including depression, anxiety, insomnia, post-traumatic stress disorder, suicidal ideation, and somatization were also significant [15–17].

Reports suggests elevated levels of loneliness during the pandemic for healthcare professionals [18]. Loneliness is prominent amongst healthcare professionals, where a combined prevalence across 101 countries was 21% during the COVID-19 pandemic in comparison to 6% before the pandemic [18]. It is a major health concern as it is a predictor of high emotional exhaustion of workplace burnout [19, 20]. Loneliness occurs when employees begin to lack meaningful social relationships regardless of the number of contacts [20]. It focuses on the quality of relationships and inconsistent expectations between desired and real social relations [20]. Loneliness and social isolation have drastic implications in the workplace, contributing to burnout and decreased job performance, creativity, organizational commitment, and work engagement [21, 22]. Work engagement is demonstrated as mediator between loneliness and organizational citizenship behaviors, which are relative to job satisfaction and employee wellbeing [21–23].

Critical care employees working in extremely difficult and high-risk conditions require urgent need for mental support [20]. Peer support is an important element and a significant work resource with positive effects on mental health [20]. It refers to the sharing of common experiences by individuals facing similar challenges and giving and receiving help based on knowledge from the shared experience [24]. Peer support can facilitate the development of decision-making, problem-solving, coping and stress management skills [25]. Supports from co-workers and friends have demonstrated reduction in emotional exhaustion, burnout experiences and loneliness [20, 26]. Maslach and Goldberg (1998) suggests that peer support groups may provide new insights, personal rewards, emotional comfort, and may contribute as a source for optimism, humor, and encouragement during difficult and stressful times [26, 27].

Problem-solving abilities significantly influences overall psychological wellbeing and social competence because the ability to resolve or cope with daily stressors is strongly affiliated to social and personal functioning [28, 29]. Problem-solving can be viewed as a self-directed cognitive-behavioral process, where individuals attempt to discover or identify adaptive or effective solutions to a problem encountered during their daily living [29]. Ineffective or maladaptive coping behavior leads to various personal and social consequences (i.e., anxiety, anger, psychological distress) [29]. Contrastingly, problem-solving skills can act as a buffering factor to attenuate the negative effects of stress [29].

Tailoring is a process of customizing to match the characteristics of individuals [30]. It is used to respect the differences amongst people, which influences attitudes and facilitates behavior change by attending to the specific needs of end-users [30, 31]. By understanding tailoring, and the aforementioned research and practice context for critical care healthcare professionals, our research team were prompted to conduct an umbrella review that sought individual interventions to improve wellbeing and decrease burnout for critical care healthcare professionals [32, 33]. This was followed by realist expert opinion paper by Adnan et al. (2022) that interviewed 21 critical care experts to describe (using theory prepositions) contextual factors and mechanisms required for an intervention to work for critical care healthcare professionals [32]. Tailoring was highlighted as an essential component in both the umbrella review and expert opinion methodologies, which enabled development and refinement of a program theory of individual-focused interventions for healthcare professionals in critical care settings [32, 33]. The authors then used the program theory to guide the design of the intervention in this study.

This study will combine the three concepts of peer support, problem-solving and tailoring to determine its effectiveness in improving wellbeing and engagement and decreasing burnout amongst critical care healthcare professionals. To the authors’ knowledge, there are no similar studies with the proposed intervention within the critical care workforce. Thus, the primary aim of this study is to test the feasibility and user-perceived acceptability of a combined Individual Management Plan (IMP) and Professional Problem-Solving Peer (PPSP) debrief in comparison to informal peer debrief. Specifically, the study will test the feasibility of the recruitment process, enrolment, intervention delivery, data collection, and completion of assessment measures in a sample of critical care healthcare professionals. User-perceived acceptability will be assessed using participant engagement to the intervention and user satisfaction. The secondary aim is to examine the preliminary effectiveness of the intervention on improving wellbeing, work engagement, and decreasing burnout. This study hypothesizes that the combined intervention will be (1) feasible (in terms of recruitment, enrolment, intervention delivery, and data collection, and completion of assessment measures), (2) acceptable in terms of participant engagement and user satisfaction, and (3) effective in improving wellbeing, engagement, and decreasing burnout symptoms than the informal peer debrief intervention at post-treatment and at the two follow-up periods (1 month and 3 months).

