### Sample size estimation

To achieve the primary aims of determining feasibility and acceptability, a pragmatic approach will be taken in that if sufficient data to address the secondary aim (preliminary effectiveness) can be achieved, this should also be sufficient for the primary aim. Power calculations were therefore conducted to determine the sample size required for the secondary aim of this study.. Analyses variance with repeated measures between and within the design in relation to the participants wellbeing was used, with low effect size estimated (η^2^ = 0.061). Significance level was 0.05 and power at 0.95. This resulted to a minimum sample of 106 participants for the study, having considered 20% attrition rate. The sample size was rounded off to 110 participants (55 each group) to enable equal samples sizes in both groups.

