Secondary outcome measures using questionnaires will be analyzed following the Intention to Treat (ITT). ANOVA or chi-square will be used to compare the sociodemographic data and baseline outcome measures (T0) [50]. Secondly, longitudinal changes (baseline, post-treatment, and 1 month and 3 months follow-up) and the differences between the two groups will be examined using mixed linear models as these models are more precise than the repeated measures of ANOVA [50]. Missing or incomplete data will be considered in the ITT analysis using maximum likelihood estimation method [50]. Effect sizes will be calculated using Cohen’s *d* (bias corrected) to represent the difference between Standard Mean Changes (MC) (T0-T2, T0-T3, T0-T4) [50]. Calculation of SMC in each group will be conducted, providing the *d* index of the general effect size from the differences between combined Individualized Management Plan (IMP) and Professional Problem-Solving Peer (PPSP) debrief vs. informal peer debrief [50]. After the data is analyzed, summary tables will be provided for all planned evaluations at pre-treatment (T0), post-treatment (T2), 1 month follow-up (T3), and 3 months follow-up (T4) [50]. Results will be reported as frequencies and descriptive statistics (mean, standard deviation, and percentages), summarizing the characteristics of the total sample and participants within each group [50].

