This protocol provides information on a randomized control trial that plans to carry out the intervention based on the combination of tailoring the intervention, peer support, and problem-solving approach on critical care healthcare professionals. The lack of evidence on the feasibility and acceptability of such concepts requires a pilot study to gain greater insight into the preparation process. It is expected that the participants assigned to the intervention group will demonstrate feasibility and user-perceived acceptability of the treatment processes, alongside statistically significant better results in improving wellbeing, work engagement, and decreasing burnout components. The outcomes in this study will be used as preliminary data for the larger and more defined randomized control trial.

One strength identified in this protocol is the inclusion of a large sample size, which is a result from the estimation of the sample size calculations. This provides an opportunity to acquire more accurate mean values, provides smaller margin or error, and identify outliers that may be present (in skewing the data) within smaller samples [52]. The use of randomization, controlled, and the use of two follow-up timepoints in the design of this study may also provide understanding of both immediate and early longitudinal patterns and outcomes of treatment changes of the intervention. A limitation of the study includes the use of an active control intervention, rather than the use of a waitlist control design. Active controls have ethical advantages as it allows the provision of care to participants that are seeking help and enables non-intervention evaluation. However, such designs may produce overestimates of the intervention’s effects and that having an active control counteract and minimize such aspects. Despite this, a greater understanding of the feasibility and acceptability of combining IMP and PPSP debrief is essential to foster a larger study that determines its effectiveness in improving wellbeing, work engagement, and decrease burnout symptoms for critical care healthcare professionals.

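### The pilot's preliminary effectiveness aim is worded as a hypothesis with expected statistical significance on three constructs at three times, and the stated 0.05 and 0.95 do not describe that claim

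*Protocol article*

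**What the plan says.** The last paragraph of the Introduction gives effectiveness as a secondary aim and calls it preliminary. The same paragraph then sets a third hypothesis: that the combined intervention will be "effective in improving wellbeing, engagement, and decreasing burnout symptoms than the informal peer debrief intervention at post-treatment and at the two follow-up periods". This covers three constructs (wellbeing, work engagement, burnout) at three times (T2, T3, T4). The Discussion goes further. It expects the intervention arm to show feasibility and acceptability "alongside statistically significant better results in improving wellbeing, work engagement, and decreasing burnout components".

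Other sections describe a more modest exercise. Study design calls the trial a pilot that looks at preliminary effectiveness. Planned analysis says that most of the analysis will be descriptive. For the questionnaires it plans mixed linear models over all times, and Cohen's d "to represent the difference between Standard Mean Changes (MC) (T0-T2, T0-T3, T0-T4").

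An error rate and a power appear once, under Sample size estimation: "Significance level was 0.05 and power at 0.95". They belong to a calculation on one construct: "Analyses variance with repeated measures between and within the design in relation to the participants wellbeing was used", with η² = 0.061.

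On the use of the results, the Discussion says: "The outcomes in this study will be used as preliminary data for the larger and more defined randomized control trial".

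**The concern.** A hypothesis that one arm is more effective, together with an expected significant result, invites a yes-or-no reading at the end of the trial. For that reading the article would have to say which comparison decides, and it does not. Hypothesis 3 spans nine construct-by-time comparisons. The 0.05 and 0.95 were set for one test on one construct.

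The scope is looser still because none of the instrument descriptions under Secondary outcomes is assigned to wellbeing, the construct on which the trial is powered. PANAS or DASS-21 could each be taken as the wellbeing measure.

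What is at stake is the conclusion drawn from the pilot. One nominally significant comparison among several could be reported as support for effectiveness. A set of mostly non-significant ones could be reported as failure of a hypothesis that the trial had little chance of confirming in full. Either would be a poor basis for the larger trial.

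**Working it through.** **Inputs from the article.** Three constructs and three post-baseline times (Introduction); level 0.05, power 0.95, η² = 0.061, 20% attrition, 55 per arm (Sample size estimation).

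**Inputs assumed.** Two-sided tests; one scale per construct; nine separate arm comparisons; normal test statistics whose correlation is the product of a between-construct part (0 to 0.7) and a between-time part (0.3 to 0.8); the η² read as a simple two-group effect. The article gives none of these.

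**The plan's own figure.** The minimum of 106 cannot be reproduced, because the article does not give the number of measurements, their correlation or the term tested. With f = √(0.061/0.939) = 0.255, power 0.95 and an assumed correlation of 0.5, the between-group effect needs 122-152 before attrition and the interaction 30-54. This does not affect the present point; it only confirms that the calculation concerns one test.

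**Reading 1: any of the nine counts.** With no true effect:
- Independent tests, either direction: 1 − 0.95⁹ = 37.0%.
- Independent tests, intervention's favour only: 1 − 0.975⁹ = 20.4%.
- Correlated tests (multivariate normal simulation over the assumed ranges): about 20-35% in either direction and 10-19% in favour. The low end is at correlations 0.7 and 0.8, the high end at 0 and 0.3.

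The nominal rates for one test are 5% and 2.5%.

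If the mixed model gives one group-by-time test per construct instead, there are three tests: 1 − 0.95³ = 14.3% if independent.

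**Reading 2: all nine must be significant.** Type I error is then no problem: under no effect the chance that all nine favour the intervention is below 0.1%. Power is the problem:
- Completers per arm: 55 × 0.8 = 44.
- Standard error of d: √(2/44) = 0.213.
- Assumed effect: d = 2f = 0.51.
- Power of one comparison at 0.05: Φ(0.51/0.213 − 1.96) = Φ(0.43) = 0.67. Joint power cannot exceed this.
- Joint power over nine, by simulation with d = 0.51 everywhere: 0.13 at correlations of 0.3 between constructs and 0.5 between times, and 0.23 at 0.5 and 0.7. Over the whole range used for Reading 1 it runs from 0.05 to 0.33.

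**Side by side.**

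| Reading of hypothesis 3 | Chance of a false claim | Power |
|---|---|---|
| Stated, one test on wellbeing | 5% | 0.95 |
| Any of nine | 20-35% (10-19% in favour) | not computed |
| All nine, in favour | below 0.1% | 0.13-0.23 (0.05-0.33 over the full range) |

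**The case against.** The strongest reply is that much of this is silence. The article neither plans nor rules out a multiplicity adjustment. Handling of secondary outcomes is commonly left to an analysis plan, which is not shown. The time-specific d values are effect-size calculations, not declared tests. That stands. A reader might infer that everything will be tested at an unadjusted 0.05, but the 0.05 appears only in the sample size calculation.

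Four further inferences also go beyond the document:
- **That a chance better result is likely.** In the favourable direction, nine comparisons give 10-19%, with a ceiling of 20.4%. That is several times 2.5%, but not likely.
- **That about 42 comparisons are in play.** Splitting every instrument into subscales (14 scales × 3 times) gives that count. Hypothesis 3, however, does not name turnover intention, practice environment or problem-solving.
- **That any single success would be read as support.** The hypothesis joins its constructs and times with an and. Read literally it needs all nine, which does not inflate error. That reading moves the difficulty to power.
- **That the largest d will size the next trial.** The article says only that the results are preliminary data, and the Abstract says that the larger trial will test efficacy.

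The reply does not remove what the article positively states: an effectiveness hypothesis and an expectation of significance, beside a preliminary and mostly descriptive pilot. A later analysis plan would leave those sentences as they are.

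**Conclusion.** The concern holds as a conflict of framing within the article. The Introduction and Discussion promise a confirmatory answer on three constructs at three times. Study design and Planned analysis describe a pilot that estimates. The article does not say which comparison decides, and neither natural reading of hypothesis 3 has the operating characteristics given under Sample size estimation: on one, 0.05 is not its error rate; on the other, 0.95 is not its power.

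The sizes rest on the assumed correlations, nine separate comparisons, 44 completers per arm and d = 0.51. The last two are simplifications, since the planned mixed model also uses incomplete records and the η² comes from a repeated-measures calculation. The direction of the result does not depend on the exact values. The feasibility and acceptability aims are unaffected. The change is cheap and worth making because it settles what the pilot may conclude about effectiveness.

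**What to change.** - **Introduction and Discussion:** restate hypothesis 3 as estimation of preliminary effects on wellbeing, engagement and burnout, and delete the expectation of statistically significant results.
- **Planned analysis:** report the arm differences from the mixed models already planned, with 95% confidence intervals at each time. Label them exploratory, and state that no effectiveness conclusion will be drawn from an isolated p<0.05.
- **Secondary outcomes:** name in advance one scale per construct, including wellbeing, whose estimate, interval and SD will inform the larger trial.

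This needs no new data or participants. The cost is a more modest claim.

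A Holm adjustment across the three constructs, on a contrast averaged over T2 to T4, is an option if the sponsor wants to keep a significance statement, but it is not required. It has a price. With an assumed correlation of 0.6 between follow-ups, the standard error is 0.213 × √((1 + 2 × 0.6)/3) = 0.183. Power at d = 0.51 then falls from about 0.80 at 0.05 to about 0.66 at Holm's first step of 0.05/3 = 0.0167. An average also does not answer a hypothesis stated at each time.
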